**c. Study Timeline**

The intervention will run in a series of three waves across four academic school years in Years 2-5 (see **Table 1**). Waves 1 and 2 (**W1** and **W2**) will each include six schools (3 intervention (INT) and 3 control (CON) schools), and Wave (**W3**) will consist of four schools (2 INT and 2 CON).

| Table 1: General design and timeline of study                                                                                                                                                                                                                                                                                     |                                                                                                                                                                                                                                                                                     |                                                                                                                                                                                                                                |                                                               |
|-----------------------------------------------------------------------------------------------------------------------------------------------------------------------------------------------------------------------------------------------------------------------------------------------------------------------------------|-------------------------------------------------------------------------------------------------------------------------------------------------------------------------------------------------------------------------------------------------------------------------------------|--------------------------------------------------------------------------------------------------------------------------------------------------------------------------------------------------------------------------------|---------------------------------------------------------------|

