| Year                                                                                                                                                                                                                                                                                                                              | Fall                                                                                                                                                                                                                                                                                | Spring                                                                                                                                                                                                                         | Summer                                                        |
| 1                                                                                                                                                                                                                                                                                                                                 | -Obtain UT-Austin and school district IRB approvals; Hold stakeholders meetings to plan implementation of Sprouts curriculum at each of the schools; Set up database; and Hire and train staff; Randomly allocate schools into INT/CON and into waves; Adapt and modify curriculum. |                                                                                                                                                                                                                                | -Build W1-INT gardens                                  |

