**Data Analyses:** Summary statistics, graphical analyses, and frequency distributions will be used to describe the data between the intervention and control groups. Data will be transformed if needed. We will handle missing data using two primary approaches: multiple imputation and full information maximum likelihood estimation methods. Each method has potential biases and makes assumptions about the underlying basis for the missing data (e.g., missing at random-MAR) and other features of the data that are present. However, we have included enough baseline variables of the participants and at the follow-up visits to make the MAR assumption plausible. Without prior knowledge of the missing data process, we will have to explore the implications of applying different strategies. **For Aim 1:** We will test if the children and parents participating in Sprouts compared to control will have increased changes in average consumption of vegetable servings per day and decreased average changes in BMI z-scores, waist circumference, fasting glucose, and insulin using well-known statistical methods for cluster randomized trials. Several analytic strategies will be employed to determine the effect of the intervention on vegetable intake and many of the other primary outcome variables. We plan to conduct a two-stage nested analysis of variance model, which is a special case of the mixed effects linear regression model also known as a repeated measures analysis of variance model. The terms in the model include the true mean for the outcome variable, the fixed effects of the intervention arm, one random cluster effect (school), and the random error term. In this case, the schools (clusters) should be regarded as nested within the intervention arms and the students or parents within the school (clusters). We will model the pattern of covariance among observations as an unstructured variance–covariance matrix because of the small number of repeated assessments. We will also explore interaction effects between intervention group and selected covariates to determine whether the intervention was more effective for some covariates. For example, we will test whether the effectiveness of the intervention varied by age, gender, race/ethnicity, baseline BMI, percent free and reduced lunches, physical activity measures, class attendance, and wave of data collection. These tests will be considered as exploratory analysis and treated as hypothesis generating and interpreted with caution. The analytic approach for the secondary outcome measures (i.e., blood pressure, percent body fat, metabolic syndrome, adipocytokines, other dietary intake variables, and related dietary psychosocial behaviors) will involve a similar use of linear mixed models. Again, school will be modeled as a random effect nested within treatment arm, and treatment arm will be modeled as fixed effects. **For Aim 2:** To test the effects of the Sprouts intervention on changes in vegetable intake and availability and on related dietary behaviors in the parents, we will use similar and well-known statistical methods as described for Aim 1. As exploratory and secondary analyses, we intend to conduct structural equation modeling (SEM) with established mediational (and direct) effects, with and without the cluster effect variables, to examine how changes in behaviors, as well as program fidelity (attendance, dosage, delivery of intervention) impacts changes in main health outcomes. For the **Exploratory Aim**, we will conduct descriptive statistics on the collected pilot data of the sustainability strategies (qualitative and quantitative data obtained via structured interviews and focus groups) on both intervention and control schools. The unit of analysis will change, as these measurements will be collected on teachers, principals, GLCs, administration staff, district directors and staff. We will obtain pilot data on the differences between intervention and control schools on the following: number of curriculum lessons taught, use and maintenance of garden, successful components/strategies implemented to sustain program, and additional material/resources/training requested, etc. This pilot data will serve to consider future projects to sustain the program and for power and sample size purposes.

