#### **e. Recruitment**

A flow chart depicting the study participants through the study appears in **Figure 1**. Sixteen elementary schools will be allocated to either TX Sprouts intervention (n=8 schools) or Control group (n=8 schools). The schools from the sampling frame average approximately 300 3rd-5th grade students for a total of 4,800 3rd-5th grade students. All participants and their parents will have to sign assent and consent forms, approved by UT-Austin's Institutional Review Board. Based on previous intervention work with Hispanic communities, we anticipate ~50% of parents will consent for their children to participate, and their children will complete all the baseline measures (n=2,400). We anticipate 15% attrition at post-intervention measurement due to parents/students moving away or being sick or absent from school, which would mean that 2,040 children (or 127 children per school) would complete the post-testing measures in one school year. Based on blood draw participation rates in LA Sprouts, we anticipate that 50% of participating children (n=1,200) will also participate in the blood draws at pre-intervention and 40% (n=960 or 60 per school) at post-intervention.

Important components of our recruitment and retention strategy developed from numerous years of research with Hispanic children/families include: 1) bilingual staff, 2) Spanish and English forms/questionnaires written at a 3rd grade reading level, and 3) incentives for participation.

We will attempt to recruit approximately 10-15 school stakeholders (i.e., teachers, principals, administration staff) and 5-10 GLCs members to conduct structured interviews with over sustainability issue. The principals at each school will likely help recruit these individuals.

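### The primary model omits wave although arms are balanced within three waves run in different school years: no bias, but any between-year variation makes the test conservative

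*Protocol*

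**What the plan says.** **Design.** Section 4.c (Study Timeline) says: "The intervention will run in a series of three waves across four academic school years in Years 2-5". Waves 1 and 2 "will each include six schools (3 intervention (INT) and 3 control (CON) schools"), and wave 3 "will consist of four schools (2 INT and 2 CON"). Table 1 gives the Year 1 task as "Randomly allocate schools into INT/CON and into waves". It places baseline and post-test for waves 1, 2 and 3 in Years 2, 3 and 4. Section 6.e (Recruitment) gives the totals: "Sixteen elementary schools will be allocated to either TX Sprouts intervention (n=8 schools) or Control group (n=8 schools").

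**Analysis.** The Data Analyses paragraph in section 5 lists the primary model terms as the true mean, "the fixed effects of the intervention arm, one random cluster effect (school), and the random error term". For secondary outcomes it repeats the structure: "school will be modeled as a random effect nested within treatment arm, and treatment arm will be modeled as fixed effects". Aim 2 (parents) is to use similar methods. Wave appears once, at the end of a list of covariates whose interaction with arm will be explored: "class attendance, and wave of data collection". Those tests are labelled exploratory and hypothesis generating.

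**The concern.** Arms are equal in number within each wave, so wave is a balancing factor of the design. A school year can differ from the next in weather for the gardens, educators, school meals or measurement teams. If such things shift the average change in a wave, they shift both arms of that wave alike and cancel from the arm difference. A model without wave does not know this. It counts the shifts as school-to-school noise and puts them into the standard error.

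With 16 schools, the school-level variance largely sets precision. The listed model could therefore report intervals wider than the design earns and test below the nominal 5% level. The same structure serves every primary and secondary outcome in both aims. The protocol lists the model terms itself, so the omission is in stated text and is not a detail left open.

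**Working it through.** **Inputs.** From the protocol: 16 schools in waves of 6, 6 and 4 with arms 3:3, 3:3 and 2:2; 127 children per school; two-sided alpha 0.05. From Table 2, vegetable intake: effect 0.5 serv/d, ICC 0.071, σ² = 0.08. Assumed: the share *f* of between-school variance in change that is due to wave.

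**Step 1: which variance is 0.08?** The Table 2 footnote and the text call it variance within schools. Two readings can be tested against the table, using schools per arm = 2(z₁₋α/₂ + z_power)² × V / 0.5², where V is the variance of a school mean.

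- Read as the child-level variance: V = 0.08 × [1 + 126 × 0.071]/127 = 0.0063. At 80% power this gives 0.39 per arm, or 2 schools in total. Table 2 says 12.
- Read as between-school variance: total = 0.08/0.071 = 1.127; within = 1.127 − 0.08 = 1.047; V = 0.08 + 1.047/127 = 0.0882. This gives 5.54, 7.42, 8.25 and 10.50 per arm, or 12, 16, 18 and 22 schools. All four vegetable-intake cells are reproduced. The parent column (64 per school, 0.51) gives 12, 16, 18 and 24, also as printed.

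The second reading is used below because it agrees with the protocol's own power table.

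**Step 2: how much wave variance enters the error.** Without a wave term, the wave contribution to the within-arm sum of squares is, per arm, σ²_wave × [8 − (3² + 3² + 2²)/8] = 5.25 σ²_wave. Over two arms this is 10.5 σ²_wave. Divided by 14 degrees of freedom it is 0.75 σ²_wave. The true variance of the arm difference contains none of it.

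**Step 3: standard errors.** With σ²_wave = 0.08*f*:

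- true SE² = (2/8) × [(1 − *f*) × 0.08 + 1.047/127]
- arm-only model SE² = the same plus (2/8) × 0.75 × 0.08*f*

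Example, *f* = 0.2: true SE = √(0.0722/4) = 0.134; model SE = √((0.0722 + 0.0120)/4) = 0.145; ratio 1.08.

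**Step 4: size and power.** School means were simulated 200,000 times per row and analysed by arm alone (14 df) and by arm plus fixed wave (12 df).

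| Wave share *f* | SE overstated, arm only | Type I, arm only | Power, arm only | Power, arm + wave |
|---|---|---|---|---|
| 0% | 0% | 5.0% | 88% | 87% |
| 5% | 2% | 4.7% | 88% | 88% |
| 10% | 4% | 4.3% | 89% | 90% |
| 20% | 8% | 3.7% | 91% | 93% |
| 30% | 13% | 3.2% | 92% | 95% |

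With wave in the model, type I error stays at about 5% in every row. Noncentral t on 12 df gives the same powers with wave: 87.0, 89.9, 92.6 and 95.1% at 0, 10, 20 and 30%.

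Arm-only power also rises with *f*, because wave variance that is part of the 0.08 cancels from the true arm difference. The gain from adding wave is therefore about 0.6, 2 and 3 points at 10, 20 and 30%.

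**Sensitivity.** If wave variance comes on top of the pilot 0.08 and makes up 10, 20 or 30% of the enlarged between-school variance, arm-only power is about 86, 84 and 81% against 87% with wave. The gains are then about 1, 3 and 6 points.

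**The case against.** **The planned analysis is valid.** It is unbiased and its type I error is at or below 5%, so the wave term only buys efficiency. This stands. A reader might infer bias or an inflated false-positive rate from a model that ignores a design factor. Equal arms within each wave rule that out as far as wave is concerned.

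**The loss may be nil.** The protocol gives no between-year variance. Outcomes are changes over one school year, so differences between years in level drop out. Schools are allocated to waves at random, so waves should not differ systematically in school mix. Below a share of about 5%, the wave term costs a little power. This also stands, and it is why the size is given only as a range.

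**The gain could be read too large.** A reader might set 88% without wave against 90, 93 and 95% with it and infer gains of 2, 5 and 7 points. The 88% applies only when wave explains nothing, so that is not a like-for-like comparison.

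**The 0.08 is labelled within-school variance.** On that label the between-school variance is about 0.006, and power for 0.5 serv/d is close to 100% with or without wave. The between-school reading is preferred because it reproduces Table 2, but the label conflicts with it. The power figures depend on that choice. The direction of the effect does not.

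**Wave is mentioned, and several analytic strategies are promised.** An interaction model would normally carry a wave main effect, but these tests are declared exploratory. No strategy named in the paragraph adjusts the primary test for wave.

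**Conclusion.** The point holds as a matter of precision. The listed primary and secondary models leave out a factor within which the arms are balanced. The arm estimate is unaffected. To the extent that change differs between school years, the interval is too wide and the test conservative.

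For vegetable intake the standard error is overstated by about 4, 8 and 13% at assumed wave shares of 10, 20 and 30%. The power forgone is small at 10% and about 2 to 3 points at 20 to 30%. It is somewhat larger if wave variance adds to the pilot figure.

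That the term is missing is certain from the text. The size of the loss is not: it rests on an assumed wave share and on reading 0.08 as between-school variance. The documents do not support a claim of material loss as fact. The change is worth making because it is cheap, and because adding wave after results are seen would be a discretionary choice.

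**What to change.** Add wave (three levels) as a fixed effect in the primary and secondary mixed models for Aims 1 and 2. State that arm is tested on 12 school-level degrees of freedom (16 schools − 1 mean − 1 arm − 2 wave). Keep the arm-by-wave interaction exploratory.

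The cost is one model term and 2 of the 14 degrees of freedom, about 1 point of power (88% to 87% for vegetable intake) if wave explains nothing. No change to the number of schools, allocation or data collection is needed.

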
## 6. Participants

### a. Target Population

This study targets communities serving primarily low-income Hispanic children, a rapidly growing population in Texas at high risk for obesity and related metabolic disease such as cardiovascular disease and T2D. More culturally appropriate interventions targeting this high-risk population are warranted. The schools from the sampling frame average approximately 300 3rd-5th grade students for a total of 4,800 3rd-

5th grade students and a parent/guardian, as a dyad. We plan to recruit a total of 2,400 students, 1,200 from intervention and control schools respectively. Based on blood draw participation rates in LA Sprouts, we anticipate that 50% of participating children (n=1,200) will also participate in the blood draws at pre-intervention and 40% (n=960 or 60 per school) at post-intervention. We plan to audio-record meetings and conduct structured interviews on approximately 100 school stakeholders and GLC members (20 from each school) to evaluate sustainability.

#### **b. Inclusion/Exclusion**

**Inclusion Criteria:** Weight status: We will attempt to obtain a sample of normal weight children (age- and sex-specific BMI<85th percentile based on CDC BMI growth charts) and overweight and obese children (BMI≥85th percentile). We will enroll students in 3rd-5th grades (8 to 11 y). We will invite both genders of parents to participate but anticipate the majority to be mothers. Hispanic Origin: This study will include all ethnicities/races; however, the selected schools are >50% Hispanic, and therefore, we expect the majority of our students and parents to be Hispanic. All school stakeholders and GLCs members will be eligible to participate.

**Exclusion Criteria:** Children or parents presently taking medication(s) or diagnosed with any disease that could influence dietary intake or body composition; previously diagnosed with any major illness since birth (e.g. chronic birth asphyxia, cancer, etc.); or having any physical, cognitive, or psychological disability that would prevent participation in the study will be excluded. Children testing positive for diabetes will be referred to [name] (Co-I on this study) for treatment. (*Note: these participants will still be eligible to participate in the study, and we will assess whether or not to include their data in the analyses*).

#### **c. Benefits**

There are no direct benefits to the subject, other than the ability to gain knowledge about how scientific research works. There may be no benefits to the participants. However, the TX Sprouts program will likely improve dietary intake and reduce obesity and related metabolic disorders. Participants will also benefit from the intense obesity and metabolic screening and will be notified if they have pre-diabetes or type 2 diabetes. Thus, the minimal risks that the subjects may be exposed to as a result of participating in this study appear reasonable, given the expected gains from the research.

#### **d. Risks**

Surveys and questionnaires: The survey and interview questions will collect data regarding dietary intake, dietary behaviors, and lifestyle behaviors, which are not expected to make the participant feel uneasy or embarrassed. We will have the children complete these questionnaires in a classroom. As described above, all of the procedures to be utilized involve minimal risk and discomfort to the subjects. However, each subject will be told at the onset of the task that he/she has the right to end the task whenever he/she wants to or feels distressed. All personnel will be CITI certified to work with human subjects.

Anthropometrics and body fat: To help minimize the participant from feeling self-conscious about these measures, we will perform them in either a private room or behind a privacy screen. We may also have the research staff wear white laboratory coats.

Fasting blood draw: Bilingual certified phlebotomists with at least two years of experience conducting research projects will be used for the blood collection. Symptoms are usually brief and are not serious and generally go away within a few minutes without treatment by simply having the participant lie down and rest. There is a slight, but possible risks of 1) Excessive bleeding, 2) Fainting or feeling light-headed 3) Hematoma, 4) Pain, and 5) Infection.

#### **e. Recruitment**

A flow chart depicting the study participants through the study appears in **Figure 1**. Sixteen elementary schools will be allocated to either TX Sprouts intervention (n=8 schools) or Control group (n=8 schools). The schools from the sampling frame average approximately 300 3rd-5th grade students for a total of 4,800 3rd-5th grade students. All participants and their parents will have to sign assent and consent forms, approved by UT-Austin's Institutional Review Board. Based on previous intervention work with Hispanic communities, we anticipate ~50% of parents will consent for their children to participate, and their children will complete all the baseline measures (n=2,400). We anticipate 15% attrition at post-intervention measurement due to parents/students moving away or being sick or absent from school, which would mean that 2,040 children (or 127 children per school) would complete the post-testing measures in one school year. Based on blood draw participation rates in LA Sprouts, we anticipate that 50% of participating children (n=1,200) will also participate in the blood draws at pre-intervention and 40% (n=960 or 60 per school) at post-intervention.

Important components of our recruitment and retention strategy developed from numerous years of research with Hispanic children/families include: 1) bilingual staff, 2) Spanish and English forms/questionnaires written at a 3rd grade reading level, and 3) incentives for participation.

We will attempt to recruit approximately 10-15 school stakeholders (i.e., teachers, principals, administration staff) and 5-10 GLCs members to conduct structured interviews with over sustainability issue. The principals at each school will likely help recruit these individuals.

